##### Attention

Attention will be assessed with the first condition of the already mentioned flanker task, where participants have to respond to the green arrow in the middle, regardless of the nature of the flanking distractor items, by pressing the right button for right-faced arrows and the left button for left-faced arrows. Both correct and incorrect (ie, missing or lack of on-time response) responses will be added, standardized as *z* scores, to create a composite total attention score. The incorrect responses will be reversed to create a variable in which a higher score represents better attention.

##### Inhibition

Inhibition will be assessed using two different tasks: (1) the second condition with red arrows of the already mentioned flanker task, which measures interference control [54] and (2) the go or no-go paradigm, which measures the inhibition of a prepotent motor response [55]. The *z* scores on both outcome variables will be added to create a composite total inhibition score for each participant. This new variable will be reversed, so a higher score represents better inhibition skills.

The outcome variable from the flanker task that will be used is the number of faults in the task with only red arrows, representing the inability to suppress an initial response. In this task, participants have to press the arrow corresponding with the opposite direction of the central arrow.

The go or no-go task consists of 2 parts. In the first part, the participant is requested to press the button as soon as a green apple, that is, a “go” stimulus, appears on the screen. In the second part, participants have to tap on the button when the green apple appears, but they have to inhibit their response when a red cross appears through the apple, that is, a “no-go” stimulus. An incorrect answer is given when the participant presses the button, and the green apple appears with a red cross. Both conditions had a practice round before the official task. The outcome measure for the go or no-go task is the total incorrect answers in part 2.

##### Working Memory

To assess the working memory construct, a visuospatial computerized task, based on the Klingberg principles for working memory, will be used [56,57]. In the Klingberg task, participants have to remember the order that a circle shifts over a 4-by-4 grid of open squares. The task consists of 2 conditions that both start with an instruction and a 4-trial practice session before the regular session. The regular session starts with a pattern of 2 circles on adjacent units and gradually increases in length and difficulty with each trial. Each trial consists of 2 patterns of the same length and difficulty. In the first condition, patterns with a green circle are presented to the participants who have to tap on the squares in the grid in the same order afterward (forward version). In the second condition, patterns of red dots are shown which participants have to tap in the reverse order afterward (backward version). When a participant taps a wrong pattern twice on a trial of the same length and difficulty, the task ends. In this study, the average number of total correct trials in the forward and backward task will be used as a measure of working memory [56,58]. A higher score represents better working memory. There is no absolute maximum score; in theory, the task can go on indefinitely.

### Process Evaluation

#### Overview

Because conducting clinical trials in the field of adults with ID and CB seems to be challenging [25], it is also important to share the practical experiences when conducting trials using a process evaluation [59]. For conducting a process evaluation, different frameworks are developed, which all focus on several process evaluation components. For this study, the following frameworks are used: the Medical Research Council guidance [59], process evaluations for cluster-randomized trials of complex interventions as proposed by Grant et al [60], and the RE-AIM (Reach, Effectiveness, Adoption, Implementation, and Maintenance) framework [61,62]. The Medical Research Council guidance and the RE-AIM framework have recently been used in the ID-research field [19,63-65].

#### Evaluation per Music Session

The music worker will ask the participant before and after each music session how he or she feels at that moment: happy, sad, scared, angry, or tired. Sheets representing 5 emoticons with associated feelings are shown to help the participant. If possible, the participant also indicates whether this feeling is little, normal, or intense. When it is too difficult for a participant to choose a specific emotion, the participant is asked whether he or she feels pleasant or nonpleasant.

Music workers will also complete a log report after each music session. The log report contains questions about that specific session: whether the session was performed according to the manual and how much time was spent on active music making.

#### Evaluation of Music Intervention

Participants in the music intervention and music workers will be asked to complete an evaluation questionnaire after the last music session. These questionnaires are designed to gain the participants’ personal views about the music intervention and their satisfaction with specific elements of it (eg, musical instruments and frequency of the sessions). The music workers will share their observations regarding behavioral, cognitive, and emotional changes within a participant during sessions.

After the last music session, caregivers will be asked to participate in a semistructured interview. This interview will focus on observed changes in the participants’ behavior and the experiences of caregivers with this music intervention study. Topics that will be covered are related to acceptability or satisfaction, reach, and context. The interviews will be recorded with the permission of the respondents and transcribed.

#### Follow-Up Evaluation

The participants in the music intervention and caregivers from participants in the music intervention will answer a few questions about the long-term use of musical activities after the last music session. For participants, this questionnaire will be conducted at T3, and for caregivers, it will be conducted 6 months after the last session.

### Sample Size Calculation

The sample size is calculated using G*Power software (version 3.1.9.7) [66]. The sample size calculation is based on a small effect size of 0.2, a statistical power of 0.95, and a type I error probability of α=.05, which results in an unadjusted sample size of 67 participants. Because cluster randomization negatively affects the power, the sample size needs to be adjusted. With the average cluster size of 2 participants per residential facility and allowing an intraclass correlation of 0.2, the adjusted sample size is 80. To allow for a dropout rate of 20% over the course of the study, we will aim at recruiting a total of at least 96 participants.

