### Data Analysis

Participant characteristics will be compared between the group receiving the individual music intervention and the group receiving CAU. Further analyses will be adjusted for any potential significant differences. The primary analyses will be undertaken on an intention-to-treat basis, and 2-sided tests will be applied at a 5% α level. In addition, per-protocol analyses will be conducted based on the sample of participants who adequately adhered to the intervention protocol by completing at least 12 of the 16 music sessions (ie, 75%), which is similar to 67% and 80% of 2 other intervention studies among adults with mild to moderate ID [67,68]. In addition, by setting the threshold at 12 sessions, we know for sure that all intervention participants followed at least 1 or 2 sessions with a focus on emotions and EF.

To minimize the number of analyses on outcome domains, the 4 different EF measures will be converted into *z* scores and, according to factor analysis, summed up into an EF domain if possible. Subsequently, to test differences in changes from baseline to follow-up between the 2 conditions, a linear mixed model analysis for each treatment variable will be used. Within each analysis, only time and the interaction between the treatment variable and time will be used [69], making it possible to adjust for the dependence of the repeated observations within the subjects. The effect of the intervention on the 2 follow-up measurements will be assessed. This analysis allows for participants with only a baseline measurement but with missing data at follow-up to be included. The normality of the residuals from the linear mixed model analysis will be visually inspected.

Secondary analyses will be performed as well. The effect of extra music interventions will be tested applying a Mann-Whitney *U* test for the between-group comparisons. The self-reported feelings before and after each music session will be compared using a Wilcoxon signed rank test.

Descriptive statistics will be used to summarize the quantitative data of the log reports, evaluation questionnaires, and the follow-up evaluation.

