## Discussion

In this paper, the design of an RCT is presented, which aims at exploring the effectiveness of and experiences with a music intervention for adults with ID and CB on various outcome measures, including CB, well-being, depression, anxiety, self-esteem, and EF. The first strength of this study is that it concerns a clustered RCT design with a sufficient sample size. The second strength is that the multisource data collection, including the use of self-report questionnaires and tests as well as proxy measures, improves the research quality. Third, because distal outcomes (measured over a longer period of time) and proximal outcomes (measured immediately after the intervention) will be used, immediate effects can be assessed too. Lastly, as qualitative data are collected alongside quantitative data, further insight into the process or mechanisms of change can be gained.

However, some limitations also have to be taken into consideration. First, blinding is not possible in the design because the nature of the intervention and the different questionnaires at the data collection points for both groups precludes blinding of the assignment for all parties involved. The absence of an active control condition might entail difficulties in ascribing possibly disclosed effects to power factors of the music intervention, such as level of attention [70]. Furthermore, there are several anticipated challenges, which are based on previous work conducting RCTs with adults with ID. These include challenges with recruiting adequate numbers, resistance to the use of control groups, assessing participants through gatekeepers (ie, the caregivers), and staff turnover that impacts the data collection [25]. The following steps to minimize attrition are considered in this study: (1) the research team follows a flexible participant-led approach to gathering all data—with contacts being at times suggested by participants and at the convenience of the facility of the participant; (2) the incentive to complete all questionnaires and tests is increased with the compliment card that participants receive after every data collection measurement; (3) caregivers will receive multiple reminders, either live, via mail, or telephone, to return the questionnaires on time; and (4) the combination of collecting data from both participants and caregivers reduces the burden for them and diminishes the impact of participant dropout or staff turnover.

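### The sample of 67 does not give 95% power for a 0.2 SD group difference: it matches about 0.8 to 0.9 SD, and power for 0.2 SD is about 12 to 20%

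*Protocol article*

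**What the plan says.** Under Sample Size Calculation, the protocol article says the calculation was done in G*Power and is "based on a small effect size of 0.2, a statistical power of 0.95, and a type I error probability of α=.05". From these inputs the article reports 67 participants before any adjustment. The total is raised to 80 for facility-level randomisation (average cluster size 2, intraclass correlation 0.2) and to a target of 96 for 20% dropout. The section does not say whether 0.2 is d, f or f-squared, which test was chosen or what correlation between repeated measurements was assumed.

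Under Data Analysis, the tests are of between-group differences in change from baseline, in a linear mixed model with effects assessed at the two follow-ups, and "2-sided tests will be applied at a 5% α level". The Results section reports 97 participants recruited, 44 of them in the intervention group. The Discussion gives as the study's first strength that "it concerns a clustered RCT design with a sufficient sample size".

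**The concern.** In a two-arm trial, an unlabelled effect size of 0.2 called small will be read as a difference of 0.2 SD between the groups. Detecting so small a difference with 95% power takes more than a thousand participants, so a total of 67 is out by a factor of about twenty on that reading.

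The stake is how the results are interpreted. A reader who accepts 95% power for a small effect, and a sample described as sufficient, would take a non-significant result as strong evidence against even small benefits on challenging behaviour, well-being or executive functioning. If the design is sensitive only to much larger differences, that inference is unfounded, and a real moderate benefit could be missed.

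**Working it through.** **Inputs from the protocol article.** Effect size 0.2, power 0.95, α = 0.05, unadjusted N = 67, cluster size 2, ICC 0.2 and dropout 20% (Sample Size Calculation); two-sided tests (Data Analysis); 97 recruited, so 44 and 53 per group (Results); three measurements (Study Design).

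**Assumption.** The correlation r between repeated measurements is not given. I use 0 to 0.7 as the main range and show 0.8 as well.

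**1. Reproducing 67.**
- *f² = 0.2, one regression coefficient.* Noncentrality λ = N·f² = 67 × 0.2 = 13.4 on 1 and 65 df. Power is 0.9501 at N = 67 and 0.947 at N = 66. This gives 67 exactly.
- *Cohen's f = 0.2, group-by-time interaction, 2 groups, 3 waves, correlation 0.5.* λ = N·3·f²/(1 − 0.5), on 2 and 2(N − 2) df. Power is 0.9472 at N = 65 and 0.9504 at N = 66. This gives 66; at N = 67 power is 0.953.
- The same interaction with 2 waves and correlation 0.6 also gives 67.

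The rest of the chain follows: design effect 1 + (2 − 1) × 0.2 = 1.2; 67 × 1.2 = 80.4, stated as 80; 80 × 1.2 = 96.

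**2. Reading 0.2 as a between-group difference in SD.** For a two-sided two-sample t test with d = 0.2, power is 0.9498 at N = 1300 and 0.9501 at N = 1302. So N = 1302, before clustering and dropout.

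**3. Translating the metrics that give 66 or 67 into SD.**
- f² = d²/4 for two equal groups, so d = 2√0.2 = 0.89.
- Three-wave interaction with group differences (0, δ, δ): f² = δ²/18, so δ = 0.2 × √18 = 0.85. A linear build-up (0, δ/2, δ) gives 0.98.
- Two-wave interaction: 0.80.
- Direct check: 67 participants (33/34) have 95% power in a t test for d = 0.89.
- Conversely, δ = 0.2 at both follow-ups in the three-wave interaction with correlation 0.5 needs N = 1160.

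**4. What the recruited sample can detect.** Effective N = 97 × 0.8/1.2 = 64.7 (29.3 and 35.3 per group). The standard error of a difference at one follow-up, in SD units, is √(1/29.3 + 1/35.3) = 0.250, multiplied by √(1 − r²) with baseline adjustment. Power is from the noncentral t. Detectable differences are normal approximations, (1.96 + 0.84) × SE for 80% power and (1.96 + 1.645) × SE for 95%.

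| r | Power for 0.2 SD | Detectable, 80% power | Detectable, 95% power |
|---|---|---|---|
| 0 | 12% | 0.70 SD | 0.90 SD |
| 0.5 | 15% | 0.61 SD | 0.78 SD |
| 0.7 | 20% | 0.50 SD | 0.64 SD |
| 0.8 | 26% | 0.42 SD | 0.54 SD |

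The noncentral t gives detectable differences about 0.01 SD larger. For a moderate difference of 0.5 SD, power is 50% at r = 0 and 79% at r = 0.7.

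**The case against.** The strongest reply is that 67 is a legitimate G*Power result. The text never says that 0.2 is a standardised mean difference, so setting 1302 against 67 compares two metrics. That is right as to the software output: nothing was miscalculated. But the section attaches the word small and 95% power to that number, and every reading found that yields 66 or 67 implies a difference of 0.8 SD or more. Naming the metric would explain the number and would still contradict the description.

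A second reply is that a journal article may leave the test family, the metric and the assumed correlation to a fuller document. If their absence were the whole complaint, it would fail. The complaint is that a printed power statement is untrue of the planned comparison, and that the Discussion builds on it.

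A third is that the 12 to 20% range depends on one follow-up and r between 0 and 0.7, and that r = 0 is unrealistic for the same scale repeated in the same person. This stands as a caution. At r = 0.8 power is 26%. If T2 and T3 were averaged with baseline adjustment, it would be 18% at r = 0.3, 26% at r = 0.7 and 34% at r = 0.8, with 0.53 to 0.36 SD detectable at 80% power. The protocol says effects at the two follow-ups will be assessed and does not say they will be averaged. No variant comes near 95%.

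Finally, recruitment is finished, so the sample cannot change. That limits the remedy to the text, but it leaves the claim itself uncorrected.

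**Conclusion.** The concern holds. A small effect of 0.2, 95% power and 67 participants cannot all be true of a two-sided comparison between two groups. A difference of 0.2 SD would need 1302 participants (1160 for the three-wave interaction at correlation 0.5) before clustering and dropout. The figure 67 corresponds to about 0.8 to 0.9 SD, or 0.98 SD if the effect builds up linearly.

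For the 97 recruited, power for 0.2 SD at one follow-up is 12 to 20%, and the detectable difference is 0.50 to 0.70 SD at 80% power and 0.64 to 0.90 SD at 95%. These figures assume the protocol's own 20% dropout and design effect of 1.2, and r from 0 to 0.7. The mismatch between label and number does not depend on r: even the most favourable case examined leaves power for 0.2 SD at about one third. The Discussion's statement that the sample is sufficient is therefore unsupported for a small effect. This must be corrected, because it governs how non-significant results will be read.

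**What to change.** In Sample Size Calculation, name the G*Power test, say whether 0.2 was f or f-squared, and give the correlation entered. State what that effect means as a between-group difference in SD, and drop the word small. Add the difference detectable with the 97 recruited after clustering and dropout, with the assumed correlation beside it. On the assumptions above this is about 0.5 to 0.7 SD at 80% power; the sponsor should recompute it with its own correlation.

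In the Discussion, replace the claim of a sufficient sample with that figure, and say that non-significant results will be interpreted through confidence intervals.

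The cost is text only, with no new participants and no change to the analysis. The stated sensitivity becomes less favourable. The article says the data have not yet been analysed, so the correction can be made before results are known.

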## Methods

### Study Design

This study is an RCT with a pretest (T1), posttest (T2, 9 weeks after T1, unless the last intervention session was not yet completed; posttest was postponed by 1 or 2 weeks until the week after the final session), and follow-up assessment (T3, 8 weeks after T2), including 2 groups of individual participants (see Figure 1). Participants belonging to the music condition will receive 16 individual music sessions within 8 to 10 weeks, and participants belonging to the control condition will receive (individual) CAU. Randomization will be performed at a facility level for 3 reasons: first, to prevent possible interference between participants belonging to both groups in a facility; second, it is deemed unethical and difficult to explain to people with ID who are assessed to the control condition that they have to wait for the music sessions, whereas fellow residents already receive them; finally, it can also promote recruitment [17]. For randomization, a computerized random number generator will be used. There is no maximum number of participants per facility. Blinding is not possible because it is clear to the caregivers, participants, and research assistants which type of intervention a participant receives. The independent research assistants are also not blinded because the participants of the music intervention have to fill in an extra questionnaire at the second and third assessment.

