## Results

Enrollment commenced in July 2021, and data collection ended in May 2023. The aim to recruit at least 96 participants has been achieved with a total of 97 participants, of whom 44 were randomized in the intervention group. Data will be analyzed after this study protocol has been accepted for publication.

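### The dropout allowance multiplies by 1.2 instead of dividing by 0.8: keeping the stated 80 after 20% dropout needs 100 recruits, not 96

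*Protocol article*

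**What the plan says.** The Sample Size Calculation section starts from "a small effect size of 0.2, a statistical power of 0.95" and "a type I error probability of α=.05" and obtains an unadjusted size of 67. It then adjusts for randomization by facility, with an average of 2 participants per facility and an intraclass correlation of 0.2, and states that "the adjusted sample size is 80". Finally it allows for 20% dropout over the course of the study and concludes that "we will aim at recruiting a total of at least 96 participants".

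The Results section reports: "The aim to recruit at least 96 participants has been achieved with a total of 97 participants". The Discussion lists the adequacy of the sample size in a clustered design as the study's first strength. On facility sizes, Study Design says: "There is no maximum number of participants per facility".

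**The concern.** A dropout rate is a fraction of the people recruited, so the number needed at the end must be divided by the fraction retained. Adding 20% of the final number gives too small a target, because 20% of the larger recruited group is then lost. The section presents 96 as the number that preserves 80 against 20% dropout, and on its own figures it does not.

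What is at stake is the accuracy of a stated design figure and of the adequacy claim that rests on it. The article says the data have not yet been analyzed, so the statement can be corrected before results are known.

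**Working it through.** **Inputs, all from the Sample Size Calculation section unless noted**

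- Unadjusted size: 67 (taken as given here)
- Average cluster size m = 2, intraclass correlation = 0.2
- Adjusted size: 80
- Dropout d = 20%
- Recruitment target: 96
- Recruited: 97 (Results)

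**Step 1. Cluster adjustment.** Design effect = 1 + (m − 1) × ICC = 1 + (2 − 1) × 0.2 = 1.2. Then 67 × 1.2 = 80.4, which the section gives as 80. This step reproduces, apart from 0.4 of a participant dropped in rounding.

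**Step 2. The plan's dropout step, reproduced.** n × (1 + d) = 80 × 1.2 = 96, exactly the stated target.

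**Step 3. The dropout step that keeps 80.** n / (1 − d) = 80 / 0.8 = 100. From the unrounded 80.4, 80.4 / 0.8 = 100.5, so 101.

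**Step 4. What remains at 20% dropout.**

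| Recruited | Remaining (× 0.8) | Against 80 |
|---|---|---|
| 96 | 76.8 | 3.2 short |
| 97 | 77.6 | 2.4 short |
| 100 | 80.0 | met |

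**Step 5. Dropout that can be tolerated while keeping 80.**

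- 96 recruits: 1 − 80/96 = 16.7% (16 losses)
- 97 recruits: 1 − 80/97 = 17.5% (17 losses)

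**Step 6. Effect on power.** The section does not name the metric of the effect size or the test used, so a model has to be assumed. The one used here is a group-by-time interaction in a repeated-measures analysis of variance with f = 0.2, 2 groups, 3 measurements, a correlation of 0.5 between measurements and α = .05. It gives 66 at 95% power, close to the stated 67. Dividing the remaining participants by the design effect:

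| Remaining | Effective size (÷ 1.2) | Power under the assumed model |
|---|---|---|
| 76.8 (96 recruited) | 64.0 | 94.4% |
| 77.6 (97 recruited) | 64.7 | 94.6% |
| 80 | 66.7 | 95.2% |

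The loss is 0.6 to 0.8 percentage points.

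**The case against.** Three arguments can be made for the stated figure.

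- **Clusters shrink as people drop out.** If the average of 2 refers to residents recruited, the design effect among those remaining is smaller. With independent 20% dropout from pairs it is 1 + 0.8 × 0.2 = 1.16, and 67 × 1.16 / 0.8 = 97.15, almost exactly the 97 recruited. Taking a uniform average of 1.6 gives 1 + 0.6 × 0.2 = 1.12 and 67 × 1.12 / 0.8 = 93.8, which 96 would cover. This is a fair point about the real shortfall. However, the section does not say whether its average is before or after dropout. It does not argue this route; it fixes 80 as the adjusted size and then inflates it.
- **The mixed model keeps incomplete cases.** The Data Analysis section retains participants with missing follow-up. Those lost between posttest and follow-up still contribute change to posttest, so counting completers somewhat overstates the loss. Participants with a baseline only add little about change, and the plan itself chose to inflate for dropout.
- **The gap is small.** It is 3 to 4 recruits. This stands, and it sets the weight of the point.

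A reader might also infer more than the documents support:

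- **That the Results section is wrong to say the aim was met.** It claims only that at least 96 were recruited, and 97 were.
- **That 102 recruits are needed.** That figure comes from rounding twice (80.4 up to 81, then 81 / 0.8 = 101.25 up to 102). Rounding once gives 101.
- **That unequal facility sizes push the requirement much higher.** A design effect of 1.2 does assume equal clusters of 2, no maximum per facility is set, and unequal sizes raise the design effect in general. But the article gives no spread of facility sizes. With an assumed coefficient of variation (CV) of 0.5, the formula 1 + ((1 + CV²)m − 1) × ICC gives 1.30 and 110 recruits. With an assumed 0.7 it gives about 1.40 and 117 to 118 recruits. These are illustrations, not findings about this trial.

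**Conclusion.** The point holds as an arithmetic error in the dropout step. The target of 96 multiplies by 1.2 where division by 0.8 was needed. The required recruitment on the plan's own figures is 100, or 101 without the intermediate rounding. At 20% dropout the 97 recruited leave about 78 rather than 80, and they protect 80 only up to about 17.5% dropout.

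This conclusion rests only on the stated 80, 20%, 96 and 97. The power figure rests in addition on the assumed model, and there the loss is under 1 percentage point. The error does not show that the trial is underpowered, and it changes no design decision. If actual dropout is at or below about 17.5%, the stated 80 is reached anyway. Whether 67 is itself the right starting number is not judged here.

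**What to change.** In the Sample Size Calculation section, show the dropout step as 80 / 0.8 = 100 (101 from the unrounded 80.4). State that the 97 recruited protect the adjusted size of 80 only up to about 17.5% dropout. Qualify the Discussion's statement on the adequacy of the sample size in the same terms. The Results sentence can stay as it is, because it correctly reports that the recruitment aim of 96 was met.

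Optionally, now that enrollment is complete and facility sizes should be known, recompute the design effect from the actual sizes and report the effective sample size. Until then, label any coefficient of variation as an assumption.

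The cost is a few sentences, with slightly less favorable figures. Recruitment should not be reopened.
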